## Abstract

**Background:**

Coronary heart disease (CHD) is the leading cause of death in the developed world, and its prevention a core activity in current UK general practice. Currently, family history is not systematically integrated into cardiovascular risk assessment in the UK, Europe or the US. Further, primary health care professionals' lack the confidence to interpret family history information and there is a low level of recording of family history information in General Practice (GP) records. Primary prevention of CHD through lifestyle advice has sometimes yielded modest results although, for example, behavioural interventions targeted at "at risk" patients have produced encouraging findings. A family history approach, targeted at those requesting CHD assessment, could motivate lifestyle change. The project will assess the clinical value of incorporating systematic family history information into CHD risk assessment in primary care, from the perspective of the users of this service, the health care practitioners providing this service, and the National Health Service.

**Methods/Design:**

The study will include three distinct phases: (1) cross-sectional survey to ascertain baseline information on current recording of family information; (2) through an exploratory matched-pair cluster randomised study, with nested qualitative semi-structured interview and focus group study, to assess the impact of systematic family history recording on participants' and primary care professionals' experience; (3) develop an economic model of the costs and benefits of incorporating family history into CHD risk assessment.

**Discussion:**

On completion of the project, users and primary care practitioners will be more informed of the value and utility of including family history in CHD risk assessment. Further, this approach will also act as a model of how familial risk information can be integrated within mainstream primary care preventive services for common chronic diseases.

**Trial Registration:**

Current Controlled Trials ISRCTN17943542

## Background

Coronary heart disease (CHD) is the leading cause of death in the developed world, and its prevention a core activity in current UK general practice[1]. Family history is a significant risk factor for CHD, with, for example, 30% of UK middle-aged men reporting a family history of CHD experiencing a 71% higher CHD rate over the next 10 years, which remained unchanged after adjusting for classical risk factors such as cigarette smoking, hypertension, and obesity[2]. Similar findings have been reported in the US [3]. European prevention of CHD guidelines recommend that family history should be used as a primary prevention approach for CHD[4], while the CDC in the US has identified CHD as one of five conditions where identification of familial risk and appropriate intervention could significantly improve health[5]. This initiative has led to colleagues at the CDC commissioning a multi-centre clustered randomised controlled trial to evaluate the utility of a robustly developed CDC family history tool and intervention software ("Family HealthWare") with US Primary Care Providers[6]. The tool appears promising but the trial will not assess the utility of incorporating family history into standard primary prevention risk assessment tools.

Currently, family history is not systematically integrated into CHD risk assessment in the UK, Europe or the US[1,7]. In the UK, patients who could benefit from primary prevention of CHD are usually identified using standard CHD risk assessment scores that incorporate age, gender, diabetes, smoking status and blood pressure levels[7]. Specifically family history collection should identify relatives with premature history of CHD. The Joint British Societies guidelines note that "a family history of premature CHD (male first degree relatives aged under 55; female first degree relatives aged under 65) increases the patient's risk by a factor of approximately 1.5" but this is not explicitly incorporated in the CHD risk prediction charts[1]. Our previous research has found that primary care professionals' lack the confidence to interpret family history information[8,9] and there is a low level of recording of family history information in General Practice (GP) records[10].

Primary prevention of CHD through lifestyle advice has sometimes yielded modest results[11] although, for example, behavioural interventions targeted at "at risk" patients have produced encouraging findings[12]. There is evidence that interventions that have targeted the family as a whole, rather than individuals, are more effective[13], and it has been reported that young individuals who were aware of their family history of CHD were less likely to smoke[14]. This evidence suggests that a family history approach, targeted at "at risk" individuals and those requesting CHD assessment, could motivate lifestyle change. However, it has been suggested that assessment of inherited risk may produce fatalism or anxiety[15], although these findings have not been corroborated in other studies[16]. Furthermore, people from different backgrounds have different understanding of the causes of heart disease; research has also discovered varied "lay models" of the risk associated with a family history of heart disease [17-19]. In light of these findings, it has been emphasized that to be effective, CHD prevention needs in-depth sensitivity to the ethnically and socioeconomically diverse patients' personal and cultural models of disease and family history [17,20]. Still, patients' interpretations of, and reactions to, incorporating family history into CHD risk assessment have not been studied. We have previously explored the psychological impact of a general family history questionnaire (FHQ)[21] and the validation of this instrument [22]. We have completed a qualitative pilot study on the feasibility of incorporating family history into CHD assessment from a risk communication point of view [23]. However, in order to inform policy the assessment of the clinical utility of using family history is now needed as a priority, alongside work such as that by the CDC Family HealthWare project, and prior to the development *de novo *of further tools[6]. This should include examination of the behavioural and psychological effects of CHD interventions using family history assessment. Moreover a better understanding of the implications of being identified as at higher risk of heart disease (due to a family history of premature CHD), for individuals from different social and ethnic backgrounds is also needed.

The project will assess the clinical value and utility of incorporating systematised family history information into Coronary Heart Disease (CHD) risk assessment in primary care, from the perspective of the users of this service, the health care practitioners providing this service, and the National Health Service. Current CHD risk assessment guidelines express CHD risk within cardiovascular disease (CVD) risk assessment, with patients divided into three broad risk categories based on the risk of CVD in the next 10 years: Average risk (less than 10% CVD risk), Moderate risk (10% to 19% CVD risk), and High risk (20% or greater 10 year CVD risk)[1].

This three-phase project will assess the clinical value of incorporating systematic family history information into the standard CVD risk assessment in General Practice, by:

1 Estimating the extra proportion of participants at high risk of CHD, who would benefit from intensive lifestyle advice and medications, when incorporating systematically collected family history into the risk assessment, in comparison with current practice.

2 Comparing changes in self-reported behaviour, anxiety and social/psychological experience, between individuals who have been allocated to either CVD risk assessment using (i) standard risk assessment complemented by systematic collection of family history or (ii) standard risk assessment alone (usual care).

Further, there will be an assessment of general practitioners' and practice nurses' views on the feasibility and acceptability of incorporating family history into routine CVD risk assessment.

To achieve these goals, the project will include three distinct phases: (1) ascertain baseline information on current recording of family information, (2) assess, through an exploratory randomised study (including quantitative measures, qualitative semi-structured interviews and focus groups), the impact of systematic family history recording on participants' and primary care professionals' experience, and (3) develop an economic model of the costs and benefits of incorporating family history into CVD risk assessment. Phase 1 will provide information on the impact of CHD family history currently available in GP records on CVD risk assessment, with which the systematic collection of CHD family history (in Phase 2) will be compared, to assess the additional value of the latter intervention. Phase 3 will assess the benefits of systematic collection through health economic analyses.

Through the above three phases it is anticipated that the following five outcomes will be evaluated:

### Outcome (1)

An estimate of the proportion of the population who are at a 20% or greater CVD risk in the next 10 years with and without inclusion of CHD family histories currently collected in GP records. [Phase 1]

### Outcome (2)

An estimate of the proportion of the population who are at a 20% or greater CVD risk in the next 10 years, comparing current practice to systematic collection of family history in the intervention practices. [Phase 2]

### Outcome (3)

A comparison of self-reported behaviour (smoking, exercise, diet), psychological impact (anxiety, fatalism), perception of health, psychological and social experience between participants who have undergone CVD risk assessment using (i) standard risk assessment alone or (ii) standard risk assessment complemented with systematic collection of family history. [Phase 2]

### Outcome (4)

An evaluation of the acceptability and feasibility to general practitioners and practice nurses of incorporating formal family history collection into their routine CVD assessment. [Phase 2]

### Outcome (5)

A cost-effectiveness analysis of systematic family history collection compared to current practice will be undertaken from an NHS primary care perspective over the trial period. Parameters for the analysis will come from phase 1 and 2 of the project, supplemented with data from the published literature where necessary. [Phase 3]

On completion of the project, users and primary care practitioners will be more informed of the value and utility of including family history in CVD risk assessment. Further this approach will also act as a model of how familial risk information can be integrated within mainstream primary care preventive services for common chronic diseases.

## Method/design and discussion

To achieve the five research outcomes the project will proceed through three distinct phases. All phases of the study received ethical approval from the Multi Centre Research Ethics Committee for Scotland.

## PHASE 1: BASELINE CVD RISK ASSESSMENT WITH/WITHOUT CURRENTLY AVAILABLE INFORMATION ON CHD FAMILY HISTORY IN GP RECORDS

During this phase, the inclusion of currently collected information about family history of premature CHD in General Practice records on CVD risk assessment will be assessed. The results of this phase will inform outcome 1. This entails a cross-sectional survey to examine the current collection and retrieval of family history data in GP manual records. The impact on absolute CVD risk scores of premature CHD family history will be informed by consensus. Using GP records, standard CVD risk assessment will be compared with risk assessment resulting from the inclusion of previously collected CHD family history in GP records.

### Methods

#### Consensus agreement

absolute risk of CHD associated with premature CHD in first and second degree relatives will be identified through expert panel and literature review using Joint British Societies' guidelines as a baseline[1]. As well as the project team, the panel will include the following experts: Cardiovascular epidemiologists [[name], Queens University Belfast (who has been involved in several prospective CHD studies and on MONICA projects for CHD), Public health genetic epidemiologist ([name], CDC), General Practitioner with a track record of assessing CHD genetic morbidity in Primary Care ([name]), Public health academic with special interest in Genetics ([name], Ottawa University) and Community geneticist ([name], Ottawa University)].

#### Outcome measures data collection

Current levels of recording of premature CHD family history in GP computer records for participants recruited in Phase 2; supplemented by data from research team's previous studies, and literature review. The calculation of CVS risk will follow current JBS 2 guidelines[1].

#### Outcome measures data interpretation

Calculate current level of recording of relevant CHD family histories in GP computer records of participants entered in phase 2; Establish baseline distribution of recruited participants with average, moderate or high CVD risk categories, (less than 10%; 10 to 19%; 20% or greater CVD risk in next 10 years) on standard CVD risk assessment[1]. Recalculate the proportion at 20% or greater CVD risk after the inclusion of family history data routinely collected in GP records.

#### Sample Size

The proportion of the population at high CVD risk (20% and greater CVD risk over the next 10 years) has been estimated to be at least 5%[24]. From our previous studies in which GP records were reviewed, between 3% and 13% fulfil Joint Society family history guidelines[1]. Based on this data it is estimated that the proportion of population at high CVD risk, after the inclusion of previously collected family history in the calculation, will increase by 1% to 6% (in the age group 30 to 65). To estimate an expected percentage of 6% with a two-sided 95% confidence interval extending from 3.5 to 8.5% a total of 347 participant GP manual records need to be reviewed. The small anticipated increase acknowledges the poor recording of this information, and the assumption that not all participants who are actually at higher familial risk will shift into the high CVD risk category.

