#### Attrition rate

One thousand four hundred patients will be invited to participate. It is estimated that one thousand participants will complete consent and baseline questionnaire, with eight hundred completing the CVD risk assessment by having the serum cholesterol test, resulting in 400 participants recruited in each arm of the study.

Further, related to secondary outcome measures, it is estimated that 60% of recruited participants will complete the 6 month questionnaire. Hence 300 participants in each arm are expected to complete the study.

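### Phase 1 names two different record sources for outcome 1 (manual and computer), leaves the relation of its 347 records to the Phase 2 participants unstated, and gives a confidence interval that ignores clustering by practice

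*Protocol article*

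**What the plan says.** Four places in the Phase 1 section bear on the source.

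- The Phase 1 introduction describes a "cross-sectional survey to examine the current collection and retrieval of family history data in GP manual records".
- Outcome measures data collection names "Current levels of recording of premature CHD family history in GP computer records for participants recruited in Phase 2", supplemented by the team's earlier studies and a literature review.
- Outcome measures data interpretation says: "Calculate current level of recording of relevant CHD family histories in GP computer records of participants entered in phase 2". Its later step, which recalculates the high-risk proportion, refers only to GP records.
- Sample Size returns to manual records: "a total of 347 participant GP manual records need to be reviewed".

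The precision target in Sample Size reads "To estimate an expected percentage of 6% with a two-sided 95% confidence interval extending from 3.5 to 8.5" per cent. It starts from a high-risk proportion that "has been estimated to be at least 5" per cent, raised by one point once recorded family history is counted.

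For Phase 2, Attrition rate expects "eight hundred completing the CVD risk assessment by having the serum cholesterol test, resulting in 400 participants recruited in each arm of the study". Study Design gives 12 pairs of practices, hence 24. The Phase 2 sample size assumes an ICC of 0.01.

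The Background makes Phase 1 the reference for judging what systematic collection adds. Outcome (2) sets current practice against systematic collection in the intervention practices. Phase 3 draws on data from both earlier phases.

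**The concern.** A manual record and a computer record are different sources and need not hold the same family history. Two analysts following different paragraphs of the Phase 1 section could therefore report different values for outcome 1, and each could say that the plan was followed. With the source open, it could also be settled after the yields are known.

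This matters because Phase 1 is the only place where the article describes estimating what family history already on file adds to the risk score. The control group is scored by the standard procedure, and the Background notes that the risk charts do not explicitly include family history. The control group therefore does not clearly supply that estimate.

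There is a second, smaller problem. The 347 is calculated as if records were a simple random sample. Both Phase 1 method paragraphs draw them from Phase 2 participants, who are grouped in practices, and the same article allows for that grouping when it sizes Phase 2.

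**Working it through.** **Source: the passages side by side**

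| Place in the Phase 1 section | Source | Number |
|---|---|---|
| Introduction | manual | none given |
| Outcome measures data collection | computer, Phase 2 participants | none given |
| Outcome measures data interpretation, level of recording | computer, Phase 2 participants | none given |
| Outcome measures data interpretation, recalculated risk | GP records, type not stated | none given |
| Sample Size | manual | 347 |

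No sentence says that both sources are searched, that one takes precedence, or that the 347 is a minimum or a subsample.

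**Precision: inputs**

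- Expected proportion p = 0.06 and half-width d = 0.025 (Phase 1 Sample Size).
- z = 1.96 for a two-sided 95% interval.
- 24 practices (Phase 2 Study Design: 12 pairs).
- ICC = 0.01 (Phase 2 Sample size). The article states it for the Phase 2 outcome, so using it here is an assumption.
- About 800 participants with a risk score (Attrition rate).

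**Step 1: reproduce the plan's figure.** n = z² p(1 − p)/d² = 1.96² × 0.06 × 0.94/0.025² = 346.7, rounded up to 347. This matches exactly, so the 347 contains no allowance for clustering.

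**Step 2: 347 records over 24 practices.** Mean per practice m = 347/24 = 14.46. Design effect = 1 + (m − 1) × ICC = 1 + 13.46 × 0.01 = 1.135. Half-width = 1.96 × √(0.06 × 0.94 × 1.135/347) = 2.66 points. The interval is about 3.3% to 8.7% instead of 3.5% to 8.5%.

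**Step 3: number needed for ± 2.5 points.** The number of practices is fixed, so extra records raise m and the design effect with it. Multiplying 346.7 by 1.135 gives 394, but that holds m at 14.46. At n = 394, m is 16.4, the design effect is 1.154 and the effective number is 394/1.154 ≈ 341, which is short of 347. Solving for n directly:

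- n = 346.7 × [1 + (n/24 − 1) × 0.01]
- n × (1 − 3.467/24) = 346.7 × 0.99
- n = 343.2/0.8556 = 401.1, rounded up to 402.

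**Step 4: all 800 participants with a risk score.** m = 33.3, design effect = 1 + 32.33 × 0.01 = 1.323, half-width = 1.96 × √(0.0564 × 1.323/800) = 1.89 points.

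**Step 5: how large an ICC the 800 can absorb.** The ± 2.5 target still holds while the design effect is at most 800/346.7 = 2.31, so the ICC can reach (2.31 − 1)/32.33 ≈ 0.04.

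Steps 2 to 5 take practices as equal in size. The Data analysis section expects recruitment to vary widely between practices, which would widen the intervals somewhat.

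**The case against.** The strongest reply is that this is a loose word in a condensed article. The 347 is a correct calculation of a minimum, the Phase 2 sample comfortably exceeds it, and the choice of subsample can be left to the full protocol. The precision loss is under two tenths of a point on a descriptive estimate, and it disappears if all 800 records are used.

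Much of this stands, and it rules out several stronger readings that a reader might draw.

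- **That 347 and 800 contradict each other.** They do not. The 347 is a required number, and the computer-record paragraphs do not say that every Phase 2 participant is covered. Only the relation between the two figures is unstated.
- **That the main trial result is at risk.** It is not. Data analysis compares the FHQ and control groups, and that test does not use the Phase 1 record source.
- **That using one source must understate current recording and inflate the FHQ's gain.** Two sources searched together cannot yield less than one. But this is an undercount only if current practice means family history found in either source, and the article does not define it so.
- **That the 3% to 13% range in Sample Size measures the problem.** It comes from earlier record reviews and is not split by manual or computer source.

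The reply does not remove the conflict of source. Condensing may leave out detail, but here the article states two incompatible things. Nor does it rescue the stated interval, which is correct only for independent records.

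**Conclusion.** The point holds in this limited form. The record source for outcome 1 is contradictory, and the link between the 347 records and the Phase 2 participants is missing. The effect reaches outcome 1, the descriptive comparison of recorded with systematically collected family history, and whatever Phase 1 supplies to the economic analysis. Its size cannot be derived, because the documents give no figure for how the two sources differ.

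The stated 3.5% to 8.5% interval is somewhat too narrow for 347 clustered records: ± 2.7 rather than ± 2.5 points, with about 402 records needed to meet the target. This rests on the Phase 2 ICC applying to Phase 1 and on roughly equal practice sizes. Recording of family history may depend on practice habit, so the true ICC could differ. This part is minor, and reviewing all 800 would settle it on the protocol's own ICC.

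**What to change.** 1. Reconcile the Phase 1 introduction, the two outcome-measure paragraphs and Sample Size by naming one primary record source for outcome 1. Apply it in the same way to a stated set of participants. The simplest choice is the computer records of all Phase 2 participants with a risk score.
2. If manual records are also reviewed, describe them as a subsample spread across the practices (347 over 24 is 14 or 15 each) and say how it is drawn. Report the yield by source, and give an either-source estimate only within that subsample. It cannot be formed for participants whose manual records are not read.
3. Restate the Phase 1 interval allowing for clustering by practice, and give the ICC as an assumption: about ± 1.9 points for 800 records, or ± 2.7 for 347.

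The cost is mainly wording. Phase 2 already plans a review of participants' computer records for prescribing, and Phase 3 plans electronic collection of resource data, so family history would be an added item in access already foreseen. Manual review would be extra work if computer records are the actual plan; the article does not show what has been resourced. The source should be fixed before any yields are seen.
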